##### Adverse events

Only adverse events meeting the standard international [37] definition of serious, or events of interest related to otitis media or nasal balloon autoinflation, solicited and via medical records, are recorded. Serious adverse events are defined as death, are immediately life-threatening, cause permanent incapacitation, result in hospitalisation or prolongation of hospitalisation, or are medically important events. Adverse events of interest related to otitis media or nasal balloon autoinflation include upper respiratory tract infection, ear discharge, tonsillitis, ear pain, hearing problems, dizziness, nose bleed, and latex allergy. Non-serious adverse events defined per protocol as unrelated to OM or nasal balloon autoinflation are not recorded. Serious adverse events and adverse events of interest are reported 6–12monthly at DSMB meetings. At final data analysis, adverse events will be coded using the International Statistical Classification of Diseases and Related Health Problems, Tenth Revision, Australian Modification 11^th^ Edition (ICD-10-AM, 11th edition) [38], and code totals tallied and tabulated, and percentages compared according to treatment group allocation.

##### Adherence to treatment

ROs will telephone parent/carers at day 3 and weeks 1–3, and 5-11 post treatment allocation, or offer a clinic of home visit, to support correct nasal balloon autoinflation technique, capture adherence data, and promote ongoing treatment adherence. Participants additionally complete a take-home daily autoinflation adherence diary, by placing a sticker in the diary each time the device is used. Reported treatment adherence will be the percentage of maximum treatment adherence for the treatment period.

##### Cost-effectiveness and quality of life

The cost-effectiveness of nasal balloon autoinflation compared to usual care will be measured using the incremental cost-effectiveness ratio (ICER). Although quality-adjusted life years (QALYs) is often used to measure cost-effectiveness, given the nature of the condition and the relatively short follow-up time of the trial, it is unlikely that QALYs will provide a useful measure of quality of life. Therefore, cost-effectiveness will be determined by the ear-related quality of life measured with the OMQ-14 questionnaire at baseline (day 0) and 1 month. The OMQ14 is a 14-question survey. For the purposes of research, scores are calculated using a weighted scoring system, with high scores indicating poorer outcomes. Medical costs, including medication and health service use, and non-medical costs, including from events related to OME and its treatment, will be calculated from data collected during trial visits. Missing cost-effectiveness data will be managed through imputation, rather than deleting observations. Sensitivity analysis will be performed using both one-way and multi-way Monte Carlo simulations.

##### Process evaluation

A process evaluation will be conducted by collecting and analysing data from interviews and written records of research meetings using a qualitative approach. Data will include minutes from the steering committee, investigator team, and community advisory groups meetings and semi-structured interviews with parent/carers and Aboriginal health service-based healthcare providers and research officers. This will allow increased understanding of the outcomes of INFLATE, as well as of the implementation of the trial and of how it is received, and allow increased understanding of trial results [39]. For the process evaluation, a framework approach to analysis will be used to promote a collaborative approach to analysing qualitative data which is useful in research teams with varying experience of conducting qualitative research [40]. In addition to the process evaluation, qualitative exploration of particular aspects of interest within the trial will be undertaken using the qualitative data generated in the process evaluation, with analysis methods determined by the research question for substudies.

The process evaluation of the INFLATE trial is being undertaken together with the WATCH trial as they run parallel in most sites, share common governance, and both examine otitis media management options [33]. This will allow a longitudinal understanding of the implementation and reception of both these trials.

### Statistical analyses

#### Primary outcome

The primary analysis will be on an intention-to-treat basis (ITT), including all children randomised using alpha = 0.05. Secondary analyses will also include per protocol and treatment received (reported by parents) analyses. Sensitivity analysis will be conducted, in which missing data will be handled using multiple imputation in order to avoid underestimation of variance known to be present in single imputation approaches [41]. The relative effect of autoinflation on the primary outcome at 1 month will be estimated using a generalised linear model for binary data with log-link function, reporting relative risks (RR) and 95% confidence intervals. Both unadjusted and adjusted RRs will be reported. Adjustment covariates will include age, sex, whether unilateral or bilateral OME at presentation, and randomisation site. Subgroup analyses of the primary outcome will also be performed by treatment reported by parents, age, and tympanogram type. The unit of analysis will be the participant, rather than the ear, although a secondary analysis will be carried out using each ear as the outcome using generalised estimating equations to account for correlation and clustering.

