#### Nasal balloon autoinflation

Nasal balloon autoinflation is designed to introduce air into the middle ear and facilitate fluid drainage. It can be performed by a person with OME, in any location, potentially offering a possible low-cost, low-risk, readily accessible, and easy-to-use alternative to ventilation tube surgery [29].

The effects of nasal balloon autoinflation on OME, measured using tympanometry and audiometry, were examined in a 2013 Cochrane review consisting of a pooled analysis of 8 small trials (7/8 studies with ≤100 participants) [30]. No statistically significant difference was shown for tympanometry changes; however, a composite measure of tympanometric or audiometric improvement showed nasal balloon autoinflation for OME was effective at more than 1 month, compared to no nasal balloon autoinflation (relative risk increase = 1.74; 95% confidence interval 1.22 to 2.50). Treatment adherence varied from 43 to 98%. There was no significant difference in adverse events between nasal balloon autoinflation and no nasal balloon autoinflation, with one study documenting ear pain with balloon autoinflation. The authors interpreted the findings as ‘favourable’ but noted that the included studies were small, and recommended further research in primary care. A subsequent study published in 2015 of 320 children (4–11 years) with unilateral and bilateral OME showed tympanometric resolution at 3 months (adjusted relative risk = 1.37, 95% confidence interval 1.03 to 1.83) in a nasal balloon autoinflation group versus no nasal balloon autoinflation group [31]. The study also reported improved ear health-related quality of life and good adherence to treatment (80% at 3 months). Another study of 45 children demonstrated improvement in hearing thresholds after 1 month (difference = dB. 95% CI) and concluded the device could be useful while children were on waiting lists for surgical treatment [32]. Although Aboriginal and Torres Strait Islander children are at increased risk of OM complications, no studies of nasal balloon autoinflation have been undertaken in this population.

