### Study population/eligibility criteria

Aboriginal or Torres Strait Islander children, attending urban or regional Aboriginal Health Services, aged 3–16 years with unilateral or bilateral type B tympanograms are eligible for inclusion. Tympanometry is conducted by a trained research officer (RO), and eligibility, including trace type, is confirmed by the treating General Practitioner (GP). Exclusion criteria include clinical confirmation of a current acute upper respiratory infection, acute otitis media, perforated tympanic membrane, or ventilation tube in situ; ear surgery booked within 1 month of diagnosis; self-reported latex allergy, recent nosebleed (at least 1 nosebleed in last 3 weeks or > 1 nosebleeds in last 6 months); self-reported or documented history of an at-risk condition (e.g., immunosuppression); previous participation in the trial; or self-reported inability to use the autoinflation device (demonstrated by the inability to blow nose).

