### Treatment groups

The intervention group uses a nasal balloon autoinflation device, Otovent® [34], in both nostrils three times daily from baseline (day 0) for up to 3 months. Participants are instructed to temporarily cease autoinflation treatment while symptomatic for no more than 5 consecutive days in the event of an upper respiratory tract infection to minimise the potential for ear pain during autoinflation. Participants cease autoinflation at 1 month if they have bilateral type A, C1, C2, or C3 tympanograms. Those with a type B tympanogram in at least one ear are asked to continue autoinflation for a further 2 months. At 3 months, participants are advised to cease autoinflation irrespective of tympanogram results.

The control group is managed according to Australian treatment guidelines (usual care) and regular follow-up with ROs, without autoinflation. General Practitioners decide usual care taking into consideration a participant’s risk of more severe forms of OM.

Antibiotics, steroids, antihistamines, decongestants, and alternative therapies are not recommended use during trial participation. All children in the intervention and control groups undergo a hearing assessment by an audiologist at either the Aboriginal Health Service or an audiology service provider. Any participants with bilateral OME or hearing impairment at 3 months are reviewed by a GP for appropriate management, including referral for ENT assessment.

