### Randomisation

Participants are randomised to the intervention or control group by the RO using an automated Interactive Voice Response System (IVRS) located at the National Health and Medical Research Council Clinical Trials Centre (NHMRC CTC), Sydney, Australia. The IVRS, accessible by telephone, uses a computer-generated randomisation sequence, enabling immediate 1:1 allocation to unblinded treatment groups. Participants and health service and WSU staff are not blinded to treatment allocation due to the nature of the intervention. Randomisation is stratified using permuted block design (block size 4), based on participating site, child age (3 to 5 years versus 6 to 16 years), and whether unilateral or bilateral OME at presentation. These strata were determined a priori given their potential association with effectiveness.

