#### Secondary outcomes

The secondary outcomes are:
i)Proportion of children showing tympanometric improvement at 3 and 6 months from baseline (OME improved by child)ii)Proportion of ears showing tympanometric resolution of OME at 1, 3, and 6 months from baselineiii)Proportion of children showing tympanometric improvement at 1, 3, and 6 months from baseline (OME improved by child — unilateral and bilateral subgroups)iv)Proportion of tympanometric deterioration from a type A or C1 tympanogram to C2, C3, or B tympanogram in non-index ears at 1, 3, and 6 months from baseline (new OME by ear — unilateral subgroup)v)3-frequency average hearing levels (pure tone threshold audiometry) at 3 months from baselinevi)Ear-related health and quality of life score (using OMQ-14 quality of life questionnaire) at day 0 and months 3 and 6vii)Adverse events up to 6 months from baselineviii)Adherence to autoinflation from day 0 to month 1 (using paper adherence diary)ix)Medical and non-medical costs of OME and its treatmentx)Qualitative exploration of parent/carer and health care provider, AMS Research Officer and AMS reference group perspectives of otitis media, research processes and the research experience including the experience of using nasal balloon autoinflation

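### One of the three primary-outcome subgroup factors, parent-reported treatment, is measured after randomisation and cannot show effect modification; 'tympanogram type' needs defining

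*Protocol article*

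**What the plan says.** Under Statistical analyses, Primary outcome, the protocol article makes intention to treat primary and then fixes the subgroup factors: "Subgroup analyses of the primary outcome will also be performed by treatment reported by parents, age, and tympanogram type". Shortly before, it lists the same information as a secondary analysis: "Secondary analyses will also include per protocol and treatment received (reported by parents) analyses".

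The Adherence to treatment section places the collection of this information after randomisation. Research officers contact families at day 3 and in weeks 1–3 and 5–11 "post treatment allocation, or offer a clinic of home visit, to support correct nasal balloon autoinflation technique, capture adherence data". Families and staff know the allocation (Randomisation). Controls receive guideline care and "regular follow-up with ROs, without autoinflation" (Treatment groups).

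On baseline tympanometry, children "with unilateral or bilateral type B tympanograms are eligible for inclusion" (Study population/eligibility criteria). The stratification factors are site, age (3–5 versus 6–16 years) and "whether unilateral or bilateral OME at presentation. These strata were determined a priori given their potential association with effectiveness". Secondary outcome (iii) reports improvement at 1, 3 and 6 months in "unilateral and bilateral subgroups". The article does not define 'tympanogram type' for the subgroup analysis.

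**The concern.** A subgroup analysis asks whether the treatment effect differs between kinds of children. The factor must therefore be fixed before allocation, so that each level contains a randomised comparison. Parent-reported treatment fails this in three ways.

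- It is a consequence of allocation. By design almost no control child is in a 'treated' stratum, so no effect can be estimated within it.
- Use is plausibly tied to prognosis. Children pause autoinflation during an upper respiratory infection (Treatment groups), and the Background lists such infection as a risk factor for otitis media with effusion. Low use may therefore mark children who would have done worse anyway, and nothing comparable is flagged among controls.
- After 1 month, use depends on the outcome. Children with no type B ear stop and the others continue. If reports from weeks 5–11 entered the variable, it would condition on the 1-month result.

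At stake is interpretation. A favourable result among reported users could be read as effect modification when it only shows which families kept using an open-label device.

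The second, smaller problem is that 'tympanogram type' allows more than one reading, so the subgroup is not fixed by the words used.

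**Working it through.** **The plan's own figure.** Inputs from Sample size and power: 35% versus 50%, 5% significance (taken as two-sided), 80% power. With pooled variance and no continuity correction:

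n = [1.96·√(2·0.425·0.575) + 0.8416·√(0.35·0.65 + 0.50·0.50)]² / 0.15² = (1.370 + 0.582)² / 0.0225 ≈ 169.3, so 170 per group.

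Power at 170 per group is 80.2%; 340/0.85 = 400; 0.50/0.35 = 1.43. All agree with the protocol, and nothing below disputes them.

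**Apparent benefit among adherers with no true effect.** Both arms improve at 35%. Let q be the share of intervention children reported as non-adherent and p their improvement rate. The intervention arm as a whole must still improve at 35%, so

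rate in adherers = (0.35 − q·p)/(1 − q).

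The values of p (20% and 25%) are assumptions; the documents give none. For q, the Nasal balloon autoinflation section says of the earlier small trials that "Treatment adherence varied from 43 to 98" per cent, and gives 80% at 3 months for the 320-child trial. I treat these as shares of children, which is also an assumption.

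| Adherence | p | Rate in adherers | Excess over controls | RR |
|---|---|---|---|---|
| 80% | 25% | (0.35 − 0.05)/0.8 = 37.5% | 2.5 points | 1.07 |
| 80% | 20% | (0.35 − 0.04)/0.8 = 38.75% | 3.75 points | 1.11 |
| 60% | 25% | (0.35 − 0.10)/0.6 = 41.7% | 6.7 points | 1.19 |
| 60% | 20% | (0.35 − 0.08)/0.6 = 45.0% | 10 points | 1.29 |

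Against the 15-point target, the excess runs from 2.5/15 (17%) to 10/15 (67%). In the same scenarios the non-adherent children show RR 0.20/0.35 = 0.57 to 0.25/0.35 = 0.71 against controls. The two strata would look like a strong interaction although none exists.

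**False-positive rates.** Here the prognosis gap g between adherers and non-adherers is set at 5 to 20 points, with adherence share a, 170 per arm, a two-sided 5% test and the normal approximation. Then p(non-adherent) = 0.35 − a·g and p(adherent) = p(non-adherent) + g.

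| Adherence | Adherers v all controls | As treated (non-adherers pooled with controls) |
|---|---|---|
| 80% | RR 1.03–1.11; 5–11% | RR 1.05–1.21; 6–25% |
| 50% | RR 1.07–1.29; 7–34% | RR 1.10–1.42; 9–60% |

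**Readings of 'tympanogram type'.** The Tympanometry box classifies traces as A, B, C1, C2 or C3. If the term means the baseline type in affected ears, there is one level (B) and no subgroup. If it means the child's baseline pattern, there are two levels, unilateral B and bilateral B, both pre-randomisation. It could also mean the type in the contralateral ear of unilateral children. The paragraph makes the participant the unit of analysis, which favours the second reading. However, the same paragraph names laterality in full as an adjustment covariate, so the author had clearer words available.

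**Precision of a laterality subgroup.** For 35% versus 50% within a subgroup holding an assumed 30%, 50% or 70% of children, power is about 33%, 51% or 65%.

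**The case against.** The best reply is that these analyses are secondary to a clearly stated intention-to-treat analysis, and that per-protocol and treatment-received analyses are common companions to it. That stands. The defect lies in listing parent-reported treatment as a subgroup factor, beside age, when the same paragraph already gives it a proper place. 'Treatment' might instead mean other therapies. The overlap with arm would then be weaker, but the factor would still be post-randomisation.

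It is also fair that the size is illustrative. The prognosis gap is assumed, and the 10-point figure needs 40% non-adherence and the lower assumed rate in non-adherers. At the 80% adherence cited for the larger trial the excess is 2.5 to 3.75 points.

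A reader might go further in three ways that the document does not support.

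- *Two of the three subgroups are invalid.* This assumes that 'tympanogram type' means the type in the index ear. The text does not say so, and eligibility speaks of unilateral or bilateral type B in one phrase. Nothing suggests that the 1-month type is meant. The term is ambiguous, not invalid.
- *Laterality has been left out.* It is not named in that sentence, but it is a randomisation stratum, an adjustment covariate and a named subgroup at 1 month in secondary outcome (iii).
- *A complier-average causal effect (CACE) must replace the per-protocol and treatment-received analyses.* That is a preference. It needs an exclusion restriction and a definition of 'complier', whereas the protocol reports adherence as a percentage.

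**Conclusion.** The point holds for one factor. Parent-reported treatment is collected after open-label allocation and, read as use of autoinflation, nearly coincides with arm. It cannot support a subgroup claim. That conclusion follows from the design and needs no assumed numbers. The possible size does rest on assumptions: with non-adherent children improving at 20% to 25% against 35% overall, the spurious advantage is 2.5 to 3.75 points at 80% adherence and 6.7 to 10 points at 60%.

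'Tympanogram type' is a lesser matter of an undefined term, with a valid baseline reading available. The concern is confined to secondary interpretation. A reader might infer that the main result or the sample size is compromised, but the intention-to-treat comparison does not use either factor, and the 340/400 calculation reproduces.

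**What to change.** 1. Delete parent-reported treatment from the subgroup list. Keep it only within the treatment-received analysis already planned, labelled exploratory and non-randomised. A CACE estimate may be added, with its assumptions and the definition of a complier stated.
2. Replace 'tympanogram type' with unilateral versus bilateral type B at baseline, if that is what is meant, so that it matches the randomisation stratum and secondary outcome (iii). If something else is meant, define it as a baseline characteristic.
3. Assess age (3–5 versus 6–16 years) and laterality each by a treatment-by-factor interaction in the primary model, and report them with the limited precision in view.

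The cost is a few lines of wording and a little analysis. No new data are needed, and the sample size and primary analysis do not change.

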#### Secondary outcomes

Generalised linear models will also be used to model secondary outcomes, with log-link function used for binary outcomes, identity link for continuous outcomes, and logarithm link for count outcomes. Secondary analyses will include per protocol and treatment received analyses. Missing data will be handled using multiple imputation, using multiple regression models approach. Separate ear-based analyses will be carried out using each ear as the unit of analysis, with generalised estimating equations (GEE) used to account for the correlation and clustering of ears within an individual. Resolution at the ear level will be deemed by a change from type B to type A or C1 at 1 month.

#### Participant retention

Patient enrolment (written informed consent obtained), randomisation, early cessation of treatment, early withdrawal, or loss to follow-up will be reported as a portion of the total number of patients enrolled. Reasons for early cessation of treatment or withdrawal will also be reported.

#### Interim analyses/stopping rules

The trial design may be modified, or the trial suspended or terminated on the grounds of safety such as a life-threatening or fatal serious adverse event (SAE), an unusual cluster of SAEs, or emerging evidence from other studies indicating the trial is unsafe. Suspension or early termination of the trial based on pre-established statistical criteria (efficacy data) to determine whether trial objectives have been met are not being employed in this trial.

### Publication and dissemination

All publications and presentations arising from INFLATE are and will be conducted and reported on in a manner supporting Aboriginal and Torres Strait Islander self-determination, and that is constructive, and respectful of the autonomy of individual Aboriginal Health Services and the communities they serve. In addition to ongoing communication with the community via community reference groups, a final trial report will be generated in lay language and disseminated to the community through the Aboriginal Health Services.

## Discussion

This trial will make an important contribution to the evidence base for the safe and effective management of OME in 3–16-year-old Aboriginal and Torres Strait Islander children. Australian guidelines recommend the use of nasal balloon autoinflation for the treatment of OME in children [29], despite limited evidence of efficacy [30]. There is no evidence to support its use among Aboriginal and Torres Strait Islander children. The INFLATE trial will fill this gap and provide evidence regarding the efficacy, safety, and cost-effectiveness of this treatment alternative in this population. The trial will assess the acceptability of nasal balloon autoinflation compared with usual care with parents and carers, health care providers, and community representatives. INFLATE will report experiences of the trial implementation and governance to inform future randomised controlled trials and research in Aboriginal Health Service settings. The INFLATE trial aims to promote multidirectional learning about ear disease, its impact on hearing, learning, and development, as well as the value of clinical trial co-design and shared Governance in the Aboriginal Health Service setting.

